### Dropout Criteria

The exclusion criteria were (1) not persisting in treatment or not following the treatment plan, (2) voluntarily requesting withdrawal, (3) having other serious concurrent diseases during the treatment process, and (4) using other treatment methods in combination.

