#### Statistical Analysis

Although the sample size calculation was based on a simplified between-group comparison at the primary postintervention time point (wk 4), the primary outcome analysis will use a longitudinal modeling framework to account for repeated measurements appropriately. A linear mixed-effects model will be used, including fixed effects for treatment group, time, and group-by-time interaction, with a random intercept specified for each participant. An unstructured covariance matrix will be prespecified to model within-subject correlations across repeated VAS measurements (baseline, and wk 1, 2, 4, and 8). Sensitivity analyses using alternative covariance structures, including first-order autoregressive and compound symmetry matrices, will be conducted to assess the robustness of the results. The data analysis was performed using SPSS (version 27.0) statistical software, and the testing criteria were as follows: *α*=.05, with *P*<.05 considered statistically significant.

Given the longitudinal design with repeated measurements collected at 5 time points (baseline, and wk 1, 2, 4, and 8), all primary and secondary continuous outcomes will be analyzed rather than with independent *t* tests or simple ANOVA, which accounts for within-subject correlation and avoids violations of the independence and sphericity assumptions inherent in traditional methods.

In each linear mixed-effects model, fixed effects will include treatment group (TNO vs TNW), time (modeled as a categorical variable), and the group-by-time interaction, with a random intercept specified for each participant. An unstructured covariance matrix will be prespecified for the repeated measures, with sensitivity analyses using alternative covariance structures (autoregressive and compound symmetry) to assess robustness. The primary estimand is the between-group difference in change from baseline to week 4 (end of treatment), which is defined a priori as the primary time point based on the sample size calculation.

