To control multiplicity, a hierarchical testing strategy will be applied. The primary end point (change in VAS from baseline to wk 4) will be tested at a 2-sided α level of .05. Secondary outcomes (JOA score, tenderness score, muscle tension, and infrared thermography) will be tested sequentially only if the preceding end point reaches statistical significance, thereby controlling the family-wise error rate. Longitudinal group-by-time interactions across all postbaseline time points will be considered exploratory.

Clinically meaningful improvement will be evaluated using responder analyses in addition to continuous outcomes. A reduction of ≥2 points on the VAS and an improvement of ≥4 points on the JOA score will be defined a priori as the minimal clinically significant difference. The proportions of responders will be compared between groups using generalized estimating equations, with effect sizes reported as risk ratios and 95% CIs.

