#### Analysis of the Primary Outcome

The primary outcomes will be evaluated at baseline, intervention 1 week, 2 weeks, 4 weeks, and follow-up. We will conduct a sensitivity analysis on missing data (intention-to-treat analysis). The primary end point is the average change in the VAS scale from baseline to week 4 (primary end point) and week 8 (durability assessment). The baseline covariates include height, gender, age, cardiovascular history, and weight. The entire outcome scale will be measured at baseline. When the distribution is normal, nonpaired *t* tests are used to compare 2 groups, and 1-way ANOVA and repeated measures ANOVA are used to compare multiple groups. Sensitivity analysis using multiple input techniques (chain equation inputs) will be included to evaluate the impact of missing data on the main results. In addition, we will compare participants randomly assigned to the TNO and TNW groups, who received treatment considered to have high fidelity allocation. The percentage of missing data is 20%, and 5 input datasets will be used for analysis, which is the recommended minimum quantity. Before conducting any analysis, investigate any missing data patterns, identify the reasons for the missing data, and investigate the patterns to determine the validity of the hypothesis.

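### Five imputed datasets for 20% missing data make a borderline sensitivity result depend on the random seed, and agreement with the mixed model would not show robustness to informative dropout (minor)

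*Protocol article*

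**What the plan says.** All references are to the protocol article.

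- **Analysis of the Primary Outcome** names the method: "Sensitivity analysis using multiple input techniques (chain equation inputs) will be included to evaluate the impact of missing data on the main results". It then puts missing data at 20% and fixes the number of imputations: "5 input datasets will be used for analysis, which is the recommended minimum quantity". Before any analysis, the team will "investigate any missing data patterns, identify the reasons for the missing data, and investigate the patterns to determine the validity of the hypothesis".
- **Statistical Analysis** gives the primary analysis: "A linear mixed-effects model will be used, including fixed effects for treatment group, time, and group-by-time interaction", fitted to VAS at baseline and weeks 1, 2, 4 and 8. The primary end point "will be tested at a 2-sided α level of .05". The robustness checks named there concern the covariance: "Sensitivity analyses using alternative covariance structures, including first-order autoregressive and compound symmetry matrices, will be conducted".
- **Sample Size Calculation** allows for 10% dropout, not 20%.
- **Dropout Criteria** include not persisting with treatment and "using other treatment methods in combination".

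**The concern.** Two separate matters arise.

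**The number of imputations.** A multiple-imputation result is itself a simulation result, and repeating it with another seed gives a slightly different estimate and p value. Five is a low number when about a fifth of the information may be missing. If the result lies near .05, the side of the threshold on which it prints is partly luck. The reader of the trial report could not tell, and an independent re-run might not reproduce the published figure.

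**What agreement would mean.** Chained-equation imputation with no departure specified treats the missing values as predictable from the observed ones, that is, missing at random. A likelihood-based mixed model on all visits does the same. If the two agree, it is tempting to write that missing data did not affect the result. That would claim more than the comparison can show, because both would be wrong together if patients with a poor unrecorded response leave. The planned look at missing-data patterns does not settle this, since observed patterns cannot separate missing at random from missing not at random.

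**Working it through.** The figure of five is a stated choice without a formula, so there is nothing to reproduce. Its properties can be computed.

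**Inputs**

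- m = 5 imputations and 20% missing (Analysis of the Primary Outcome).
- Two-sided α = .05 (Statistical Analysis).
- Planned difference 0.96, SD 1.37, 50 per group (Sample Size Calculation).
- Fraction of missing information λ: not given. Assumed 0.2, with 0.1 and 0.3 as the range. Simulation with 20% missing at week 4 and assumed within-patient correlations of 0.3 to 0.7 gave 0.17 to 0.21.

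**Step 1: simulation error of the pooled estimate.** Under Rubin's rules, with total variance T, the between-imputation variance is B = λT/(1 + 1/m), and the Monte Carlo SE is √(B/m). In units of √T, for λ = 0.2 and m = 5: B = 0.2/1.2 = 0.167, and √(0.167/5) = 0.183.

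**Step 2: range of printed p values for a borderline result.** Take z = 1.96 ± 1.96 × Monte Carlo SE. For m = 5 this is 1.96 ± 0.358, or z from 1.602 to 2.318.

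| λ | m | Monte Carlo SE / SE | p range around .05 |
|---|---|---|---|
| 0.1 | 5 | 0.129 | .027 to .088 |
| 0.2 | 5 | 0.183 | .020 to .109 |
| 0.2 | 20 | 0.098 | .032 to .077 |
| 0.2 | 50 | 0.063 | .037 to .066 |
| 0.3 | 5 | 0.224 | .017 to .128 |

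If λ is defined without the finite-m correction in T, the m = 5 figure at λ = 0.2 is 0.196 instead of 0.183. The message is the same.

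**Step 3: check by simulation.** Settings: 50 per arm, SD 1.37, 20% missing at week 4, correlation 0.5 assumed. For datasets whose p value with many imputations is near .03, the central 95% range of p over seeds was .010 to .101 at m = 5, .018 to .052 at m = 20 and .021 to .042 at m = 50. The share of seeds giving p ≥ .05 was 25%, 5% and 0.9%.

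**Step 4: the same check at the planned effect.** With 20% missing, 40 per arm are observed. SE = 1.37 × √(2/40) = 0.306, and z = 0.96/0.306 = 3.13. Applying ± 0.358 gives z from 2.78 to 3.49, or p from about .0005 to .006, which does not reach .05. In simulation at the design effect, about 0.1 to 4% of re-runs disagreed on significance. The relative efficiency of m = 5 is 1/(1 + 0.2/5) = 96.2%, so little precision is lost.

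**Step 5: imputation against likelihood.** In the same simulation setting, imputation with m = 50 and direct likelihood gave estimates that correlated 0.998, with a mean absolute difference of about 0.013 VAS points. When dropout was made to depend on unobserved week 4 VAS in the oil arm (an assumed mechanism), both averaged −1.157 against a true −0.96, and −0.195 against a true 0. The size of that bias belongs to the assumed mechanism. The agreement of the two methods held with and without it.

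**The case against.** The strongest reply is that little hangs on this. The confirmatory test and the hierarchy of secondary tests rest on the mixed model, which has no seed. Sensitivity analyses are usually read by estimate and interval. The wide p range applies only to a result at the threshold, and step 4 shows a stable conclusion at the planned effect. The 20% figure is also loosely worded, and the sample size section plans for 10% dropout; the λ = 0.1 row is milder. All of this stands, and it makes the point minor. It does not make five a good choice, since a larger number costs almost nothing in a trial of 100 patients.

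On the second matter, a reader might infer that the trial has no means of examining informative dropout, or that the dropout criteria show that such dropout will occur. The document supports neither. A statistical analysis plan, not shown, may contain a tipping-point analysis, and an article commonly leaves that detail to it. The dropout section does not say that outcome collection stops when a criterion is met, and the link between those criteria and poor response is plausible but not documented.

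The primary outcome section also names t tests and ANOVA, and imputation would add something to a complete-case t test. It adds little to the mixed model that the article sets as the primary analysis. The baseline covariates listed there could enter the imputation model, but conditioning on them would still not test missing at random.

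**Conclusion.** The point holds at minor severity. Five imputations leave a simulation error of about 18% of the standard error if λ is about 0.2 (13% at 0.1, 22% at 0.3). That is enough for a borderline sensitivity result to change sides of .05 with the seed. The loss is one of reproducibility in a supportive analysis, not of power, and it does not touch the primary test. It would be wrong to conclude that the trial's main finding depends on a seed.

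The second part is a limit on interpretation. It assumes default chained-equation imputation, since the article names no departure from missing at random. On that reading, agreement with the mixed model is expected whether or not dropout is informative, and so is no evidence on that question.

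**What to change.** 1. Replace the five imputed datasets with a larger number, for example 50 (20 would already cut the Monte Carlo SE from 0.183 to 0.098 of the SE), and record the seed. This costs minutes of computing.
2. State that agreement between the imputation and the mixed model will not be presented as robustness to informative dropout. This costs one sentence.
3. If the statistical analysis plan does not already contain one, add a delta-adjusted version of the same imputation: make the imputed week 4 VAS of patients with missing values progressively worse, in the oil arm and then in both arms, and report the shift at which the week 4 conclusion changes. The step size is for the trial team to choose and prespecify. This costs one extra table and no new data.

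The Results section says that formal analysis has not begun, so on the article's account all three can still be prespecified.

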#### Analysis of Secondary Outcomes

Refer to the primary outcome analysis and conduct a secondary analysis of the outcomes. We will test the interarm differences for each specified end point. AE analysis was performed using the chi-square or Fisher exact test.

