**Objective:**

This study aims to evaluate the efficacy and safety of Tuina therapy combined with medicated oil in treating NSLBP.

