**Methods:**

One hundred participants will be enrolled and randomly allocated to either a TNO group (n=50) or a Tuina combined water group (n=50). Treatment will last for 4 weeks, with sessions 3 times a week, followed by a 4-week follow-up. The visual analog scale score is the primary outcome; secondary outcomes include the evaluation of treatment Japanese Orthopaedic Association scores, infrared thermography, muscle tension tests, and tenderness scores. All adverse reactions will be recorded.

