#### Safety Evaluation

The category and severity of adverse events (AEs) after each intervention are recorded in detail on the CRF, including drug allergies, subcutaneous bleeding, joint injuries, hypertension, headache, dizziness, tinnitus, fever, and other relevant conditions. The incidence of AEs will be reported as the proportion of AEs to the total number of treatments. If the AE does not improve after sufficient rest, participants should receive timely medical treatment. Suppose a serious AE occurs, the chief investigator and the ethics committee will be well-informed within 24 hours of the event. They will be knowledgeable for additional assessment and treatment and decide whether to terminate the trial. Researchers also continue to monitor patients who have experienced AE until the issue is settled, especially individuals who withdrew due to AE. If AE is proven to be related to the intervention measures in this study, participants will receive appropriate medical and economic compensation.

The medicated oil used in this study contains ingredients with known warming or irritant properties (methyl salicylate, menthol, and processed *Aconitum* species). A multilevel monitoring strategy has been implemented to ensure participant safety. First, FEMO is a government-approved proprietary Chinese medicine manufactured under good manufacturing practice standards, with strict control of potentially toxic constituents, and is approved exclusively for external use.

During each treatment session, participants are actively observed by trained Tuina physicians for any signs of abnormal local skin reactions (excessive erythema, burning sensation, pain, or discomfort at the application site). The observations are systematically documented using tenderness scores, muscle tension tests, and structured patient feedback and are collected at predefined time points.

Infrared thermal imaging is used as an objective tool to monitor local skin temperature changes. Moderate temperature elevation is considered a physiological response reflecting improved microcirculation; disproportionate or excessive temperature increases may indicate abnormal inflammatory or irritant responses.

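### The only stated between-group safety analysis is a chi-square or Fisher test with no effect estimate: weak for modest excesses if run on participants, invalid if run on treatment sessions

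*Protocol article*

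**What the plan says.** The Objective section of the abstract puts safety beside efficacy: "This study aims to evaluate the efficacy and safety of Tuina therapy combined with medicated oil in treating NSLBP". Safety Evaluation says that the oil "contains ingredients with known warming or irritant properties (methyl salicylate, menthol, and processed *Aconitum* species"), and requires adverse events to be recorded after each intervention. The control arm receives water in place of the oil.

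For the comparison between arms, Analysis of Secondary Outcomes has one sentence: "AE analysis was performed using the chi-square or Fisher exact test". The general criterion in Statistical Analysis applies, "with *P*<.05 considered statistically significant". The article does not say whether the adverse-event test is one- or two-sided; the primary end point "will be tested at a 2-sided α level of .05".

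Two further statements bear on how that test would work. Patients are "randomly allocated to either a TNO group (n=50) or a Tuina combined water group (n=50"). And Safety Evaluation defines the incidence measure: "The incidence of AEs will be reported as the proportion of AEs to the total number of treatments". With 12 sessions per participant (Observation Group section), that denominator is up to 600 per arm.

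For binary efficacy outcomes the article goes further. In Statistical Analysis, VAS and JOA responder proportions are to be compared with a risk ratio and its 95% CI. No effect measure or interval is stated for adverse events.

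**The concern.** A significance test answers whether chance alone could explain a difference. The safety objective asks how large an excess of reactions the oil may cause, and a P value does not answer that when events are few and the trial was sized on VAS.

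The unit of the test is also unclear. The sentence on the test names none, and the only incidence measure defined uses treatments as its denominator. If the test is run on participants, a modest but real excess of skin reactions could well come out as non-significant. If it is run on sessions, a patient who reacts repeatedly counts several times as if each reaction came from a different person, and the P value can be too small. Either way, the one comparative safety result that the article provides for would be a poor basis for a statement about harm.

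**Working it through.** **Inputs from the article.** 50 per arm; 12 sessions each, so 12 × 50 = 600 sessions per arm; α = .05, taken as two-sided by analogy with the primary end point. The article gives no expected event rate, relevant excess, margin or power for safety, so there is no safety figure of its own to reproduce. The rates below are assumptions.

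**Step 1: power on participants.** Let X (oil) and Y (water) be independent Binomial(50, p) counts of participants with at least one reaction. Power is the sum of Pr(X = a)·Pr(Y = b) over all pairs (a, b) with P < .05. The mixed rule uses Fisher when an expected count is below 5 and uncorrected chi-square otherwise.

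| Water vs oil | Excess (points) | Fisher | Chi-square | Mixed rule |
|---|---|---|---|---|
| 2% vs 10% | 8 | 19% | 38% | 21% |
| 0% vs 10% | 10 | 38% | 75% | 38% |
| 2% vs 12% | 10 | 31% | 51% | 35% |
| 5% vs 15% | 10 | 24% | 39% | 35% |
| 10% vs 20% | 10 | 20% | 30% | 30% |
| 2% vs 15% | 13 | 51% | 69% | 57% |
| 0% vs 15% | 15 | 78% | 95% | 78% |
| 5% vs 20% | 15 | 51% | 66% | 64% |
| 10% vs 25% | 15 | 41% | 53% | 53% |
| 2% vs 20% | 18 | 78% | 89% | 84% |

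For excesses of 8 to 10 points the mixed rule detects 21-38%. From 13 points upward it detects more than half.

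**Step 2: what a non-significant result leaves open.** Take 5/50 on oil and 1/50 on water. Fisher gives P = .20 (uncorrected chi-square P = .09). The difference is 0.10 − 0.02 = 0.08. The Wilson limits are 0.0435 to 0.2136 for 5/50 and 0.0035 to 0.1050 for 1/50. The Newcombe interval combines them:

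- lower: 0.08 − √[(0.10 − 0.0435)² + (0.1050 − 0.02)²] = −0.022
- upper: 0.08 + √[(0.2136 − 0.10)² + (0.02 − 0.0035)²] = +0.195

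So P = .20 goes with an excess of anywhere from −2.2 to +19.5 points. With no events in an arm, the exact two-sided 95% upper limit on its risk is 1 − 0.025^(1/50) = 7.1%.

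**Step 3: the same patients counted by session.** Fisher P values, with 600 sessions per arm and every affected patient reacting once or twice:

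| Affected patients (oil vs water) | On participants | One reaction each | Two reactions each |
|---|---|---|---|
| 5 vs 1 | .20 | 5/600 vs 1/600: .22 | 10/600 vs 2/600: .038 |
| 7 vs 1 | .059 | 7/600 vs 1/600: .069 | 14/600 vs 2/600: .004 |

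The number of affected patients is the same along each row. The P value falls only because repeat reactions are counted as independent observations.

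**The case against.** The strongest reply is that an effect measure and interval for adverse events is commonly left to the full protocol or SAP, neither of which is shown. That stands as far as the bare absence of an interval goes. What remains is that the article does fix a method for the safety comparison, and fixes a denominator elsewhere that does not suit it. It also gives an effect measure with interval for responders, so this level of detail was within its scope.

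Second, the test is not the only safety output. Category, severity, incidence and follow-up of events are all to be recorded or reported. That is right; the point is limited to the comparison between arms.

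Third, a reader might infer that the plan will take a non-significant test as proof of safety. The article nowhere says so.

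Fourth, a reader might infer that the test would miss any relevant excess most of the time, whatever the denominator. The documents do not support that. They give no event rate and define no relevant excess. Power exceeds one half in most scenarios of 13 points or more, and uncorrected chi-square reaches 75% for 0% vs 10%. On the session denominator the 50-per-arm power figures do not apply at all, and repeat reactions push the test towards too many significant results.

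Finally, low power for adverse events is usual in a trial of 100 patients, and reporting an interval adds none. That is true, but an interval shows the imprecision that a P value hides.

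**Conclusion.** The point holds in a conditional form. The one between-group safety analysis that the article states serves the safety objective poorly under either reading of its unit.

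- On participants, power is 19-38% by Fisher and 38-75% by uncorrected chi-square for 2% vs 10%, 5% vs 15% and 0% vs 10%. It is 51-89% across the two tests for 5% vs 20% and 2% vs 20%. A non-significant P value is therefore weak evidence about modest harm.
- On sessions, the independence assumption fails whenever a patient reacts more than once, and identical patients can give P = .059 or P = .004.

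The power figures rest on assumed rates, a two-sided .05 test and all 50 participants per arm being analysed. The session examples assume 12 completed sessions each and the stated number of reactions per affected patient. This is an inexpensive improvement to the analysis, not an error that threatens the trial's primary result.

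**What to change.** In Analysis of Secondary Outcomes, replace the sentence on adverse events with text to this effect:

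- The unit is the participant. Participants with at least one adverse event and, separately, participants with at least one local skin reaction will be compared by the risk difference (TNO minus TNW) with a 95% confidence interval (Newcombe or exact).
- Where an arm has no events, the exact two-sided 95% upper limit will be given (7.1% at 0/50).
- The chi-square or Fisher P value is descriptive, and a non-significant result will not be read as evidence of equal risk. The safety conclusion will quote the largest excess that the interval does not rule out.
- The rate per treatment will be reported as a description only and not tested as if sessions were independent.

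The cost is a few sentences and a few lines of code. The data are already recorded after each intervention, and the Results section says formal analysis has not begun. The price is a more cautious safety statement, because the interval will be wide at 50 per arm.
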